### Study sites and settings

In India the feasibility trial will be conducted at the National Institute of Mental Health and Neurosciences (NIMHANS), Bangalore, a tertiary care neuropsychiatric institute. In Pakistan the feasibility trial will be conducted at the Institute of Psychiatry (IoP), Rawalpindi.

### Study Population

Outpatients with SMI seeking care in either of the participating mental health institutions.

### Eligibility

#### Inclusion Criteria

- Adults (≥18 years old) with SMI (i.e. schizophrenia, schizoaffective disorder, bipolar affective disorder, psychosis, severe depression with psychosis)
- Considered to be stable by the mental health clinical team
- Self-reported current smoker of any form of smoked tobacco product (including cigarettes, bidis, waterpipe etc) for at least 6 months
- Smoking on >25 days in the past month
- Able to provide informed consent
- Attending / remotely accessing services from included institutions during the study period
- Willing to cut down or quit smoking
- Willing and able to attend up to 15 face-to-face and/or remotely delivered counselling
- Living in the Rawalpindi district in Pakistan, and in Bangalore urban and rural districts in India

#### Exclusion Criteria

- Pregnant or breastfeeding women
- Comorbid drug and/or alcohol problems

### Recruitment

Patients from NIMHANS, Bangalore, India and IoP, Rawalpindi, Pakistan who are diagnosed with SMI (schizophrenia, schizoaffective disorder, psychosis, bipolar disorder, depression with psychotic symptoms) and are current smoked tobacco users, will be referred to the study team by their care team. A screening form based on the eligibility criteria (*see section 5.4.*) will be used to identify eligible participants.^44^ All recruitments to be done through face-to-face mode.

Participants from the IMPACT survey (i.e., a currently ongoing survey led by members of our study team and gathering data on the physical comorbidities and lifestyle-risk behaviours, including smoking, among people with SMI in India and Pakistan), who are smokers and have agreed to be contacted for future studies, will also be contacted and asked if they wish to participate in the study. In such a case the recruitment will happen remotely due to the restrictions imposed by the pandemic, i.e., on telephone or on video-call based on the convenience of the participant. The process of obtaining informed consent and the verbal consent provided will be audio/video recorded in such instances.

### Eligibility assessment

Each participant will be allocated a unique screening number. In addition, the following anonymised individual information will be collected and stored in a secure study database: age; gender; SMI diagnosis; current smoking status; eligibility criteria; and time taken for screening. For those identified as not being eligible for the study, the reason for exclusion will also be recorded.

Individuals who meet the eligibility criteria will be invited to participate in the study. They will receive a detailed study information sheet including the following information: the purpose of the feasibility study; the study procedures including details of interventions, process of randomisation, the collected information and the frequency and timing of data collection, breath CO monitoring; the potential benefits or risks of participating in the trial; information on privacy and confidentiality of the participants’ data, and how it will be processed; and participant’s rights, including voluntary nature of the trial and the right to discontinue participation at any time in the trial without any consequences. The information sheet will also provide contact details of a research team member in case they wish to seek more information or clarity. In the circumstance that a potential participant is unable to read or write, the researcher will provide facilitation by reading out the information sheet to both the participant and the carer if present and will respond to their queries. Participants will be given 24 hours to discuss the information with family members or friends before making a decision if they require it.

### Consent

Informed consent will be obtained before any study specific baseline assessments. Once the participants are familiar with the intent and purposes of the study, and have clarified their queries with the researcher, those willing to participate will be invited to provide written consent. For the face-to-face recruitment, we will follow a written informed consent procedure where each participant will provide their full name and signature or, if they cannot write, a thumb impression (with a witness present) as allowable according to the ethics requirements. We will follow a formal informed consent procedure where each participant will provide their full name and signature or, if they cannot write, a thumb impression (with a witness present) as allowable according to the ethics requirements in India and Pakistan. One copy of the consent form will be securely stored in a locked filing cabinet at the trial sites in India and Pakistan, separate from the rest of the trial data. Each study participant will get a copy of their signed informed consent form, and the information sheet to take home for their records. For participants who would be recruited remotely, a researcher will first read out the participant information sheet to sensitize them adequately about the purpose, procedures involved in the 4S study, participant roles and their rights, and other important ethical aspects. Afterwards, a consent form will be read out to each participant confirming their awareness about the study, their voluntary participation, confidentiality, compensation matters, and usage of the research data. Having confirmed their understanding and awareness of the study, their verbal consent will be sought, and audio/video recorded.

All consenting individuals will be registered in a secure study database, using their name, age, address, and unique study ID (*see section 5.10. for the procedure for allocating study IDs*). Only the principal investigators, country investigators, trial coordinators, and researchers involved in collecting, quality checking and entering data will have access to these identifiable data at any stage of the trial mainly to facilitate participant follow-up. Identifiable data will be stored separate to the baseline and follow-up data. For the purpose of baseline and follow-up data collection and conducting analyses, only the unique study IDs will be used, thereby ensuring anonymity of data.

### Withdrawals

Participants will be free to withdraw consent and leave the trial at any time without giving a reason. Information (written/verbal) on who to contact if they wish to withdraw from the trial will be provided to all participants. Written information on who to contact if they wish to withdraw from the trial will be provided to all participants. They will be able to withdraw by letting any member of the research team know that they wish to do so. If a participant withdraws consent to participate, no further data will be collected from them. However, data collected up to the point of withdrawal will be retained and used in the analysis, except where withdrawal of consent for the use of this data is explicit, in which case all data will be destroyed.

### Reimbursements

Participants will not be offered any personal incentive for taking part in the trial. However, at every visit for receiving the 4S intervention session or collecting bupropion/nicotine gums, each trial participant will receive reimbursement of actual travel cost. In addition, they will receive INR 250 (India)/PKR 500 (Pakistan) as compensation for time spent. The amount of reimbursement will be reviewed by the local/National Ethics Review Boards as per local prerequisites.

### Randomisation procedure

Those eligible participants who consent will be allocated a study ID and randomly assigned to one of the trial arms using a computer-generated blocked stratified (by country) randomisation sequence created using Stata version 15 (or later) with an allocation ratio of 1:1. A statistician based at the University of York, who is not involved in the recruitment of trial participants, will generate the randomisation sequence and produce the opaque sealed envelopes as detailed below.

### Trial arm allocation

Participants will be allocated to trial arms using opaque sealed envelopes stored securely at the central research office. After a participant has provided written informed consent, a researcher will make a phone call to the country specific trial manager who will be based at the central research office. Upon being provided with basic participant information, the trial manager will allocate the next envelope in the sequence to the participant. Up until this point, both the trial manager and the research officer will be unaware of the trial arm associated with the envelope. After opening the envelope, the trial manager will indicate to the researcher whether the participant will receive the IMPACT 4S intervention or brief advice and the envelope number and allocation will be recorded on the participant record. For the participants who are recruited remotely, the researcher may inform them on the same day about results of trial arm allocation over phone if they agree to be contacted again on the same day. If the participant did not agree to be contacted again on the same day, they will be informed about the trial arm allocation on a mutually agreed upon day and date for the next telephonic call.

### Blinding

Blinding the participants and clinicians from knowing who is receiving the IMPACT 4S intervention or BA is not feasible. Outcome data collection and data analysis will also not be fully blinded.

### Measures to avoid/ minimising bias

The process of randomisation will minimise the chance of selection bias. In order to minimise loss to follow-up, participants will be requested to inform the trial team of any relevant changes, for example if they plan to relocate or their contact details change. Researchers will also be in regular contact with the participants via the phone. Participants will be informed about follow-up prior to the date. Information materials in the appropriate language will be provided to ensure participants understand clearly what the expectations would be if they decide and give consent to participate in the trial.

### Study outcomes

The study will focus on the following primary (feasibility and acceptability) and secondary outcomes.

#### Primary outcomes

1. Recruitment rates: Quantitative assessment of the acceptability of the research will be assessed by numbers screened, number eligible and those agreeing to participate.
2. Reasons for ineligibility/non-participation/non-consent of participants.
3. Length of time required to achieve the required sample size.
4. Retention in study: Assessed as a proportion of those enrolled in the study who are successfully followed-up at six months.
5. Retention in treatment: Evaluated by number of study intervention sessions attended as one measure of the feasibility and acceptability of the trial interventions to participants.
6. Intervention fidelity during the delivery of the behavioural support within the IMPACT 4S intervention, as well as for BA, assessed as one measure of feasibility of intervention delivery.
7. Smoking cessation pharmacotherapy adherence: For those in the IMPACT 4S arm, adherence to smoking cessation pharmacotherapy will be assessed as one measure of the feasibility and acceptability of the smoking cessation pharmacotherapies to participants.
8. Data completeness: Data will be checked for completeness as another measure of acceptability and feasibility of data collection methods, and to identify problem areas and solutions.

#### Secondary outcomes

1. Self-reported or family/carer reported continuous smoking abstinence for at least six months (only five instances of smoking allowed during the total six months) which is biochemically verified by CO concentration (CO concentration <7ppm) at six months follow-up.^45^ This will be assessed at the longest possible follow-up point for those participants where it might not be possible to have a six months follow-up.
2. Point abstinence, defined as a self-report or family/carer report of not smoking in the previous seven days, assessed at one, three and six months follow-up. This will be assessed at the longest possible follow-up point for those participants where it might not be possible to have a six months follow-up.
3. Cost of delivering the IMPACT 4S and the BA interventions.

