**Summary**

| Title | IMPACT Smoking cessation support for people with severe mental illness in South Asia (IMPACT 4S): a protocol for a randomised controlled pilot and feasibility trial for a combined behavioural and pharmacological support intervention |
| --- | --- |
| Short Title | IMPACT 4S pilot and feasibility trial |
| Version | V 1.3 |
| Date | 22/03/2021 |
| ISRCTN | ISRCTN34399445 |
| Study design | Randomised controlled pilot and feasibility trial |
| Study duration | 36 months (twenty-four months adaptation, nine months recruitment + follow-up, three months data analysis and report writing) |
| Population | Adults with severe mental illness (i.e. schizophrenia, schizoaffective disorder, bipolar affective disorder, psychosis, severe depression with psychosis) |
| Setting | Mental health facilities in India and Pakistan |
| Treatment(s) | *Brief advice*: five minutes, face-to-face, one-to-one smoking cessation counselling session and an information leaflet.  *Combined behavioural and pharmacological support intervention (IMPACT 4S intervention)*: The intervention comprises of up to 15 one-to-one and/or remotely delivered smoking cessation counselling sessions, each lasting between 15-40 minutes and spread over three/four months, breath carbon monoxide monitoring and feedback, pharmacotherapy (bupropion and/or nicotine replacement therapy), and an information leaflet. Remote sessions can be delivered using a number of different options such as telephone or video platforms (e.g. What’s App, messenger, Zoom etc.). |
| Study aim | To adapt an evidence based, combined behavioural and pharmacological support intervention for smoking cessation among people with severe mental illness; and test the feasibility of delivering and evaluating it in India and Pakistan. |

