| Main inclusion/ exclusion criteria | Inclusion Criteria  - Adults (≥18 years old) with SMI (i.e. schizophrenia, schizoaffective disorder, bipolar affective disorder, psychosis, severe depression with psychosis) - Considered to be stable by the mental health clinical team - Self-reported current smoker of any form of smoked tobacco product (including cigarettes, bidis, waterpipe etc) for at least 6 months - Smoking on >25 days in the past month - Able to provide informed consent - Attending / remotely accessing services from included institutions during the study period - Willing to cut down or quit smoking - Willing and able to attend up to 15 face-to-face and/or remotely delivered counselling sessions - Living in the Rawalpindi district in Pakistan, and in Bangalore urban and rural, nearby/neighbouring districts in India.  Exclusion Criteria  - Pregnant or breastfeeding women - Comorbid drug and alcohol problems |
| Estimated period of recruitment | 6 months |
| Total duration per participant | 6 months |
| Statistical methodology | Quantitative analysis will focus on descriptive summaries. For each group the numbers of individuals approached, randomly assigned, receiving intended treatment, completing the study protocol, and providing outcome data will be summarised.  The number of individuals withdrawing from the intervention and/or the trial, and where available, the reasons for withdrawal, will be summarised by trial arm.  For each data collection point the number of non-responders will be calculated and attendance rates compared.  A CONSORT diagram will be provided to display the flow of participants through the study. |
| Sponsor | University of York |
| Funder | National Institute of Health Research [Grant reference number 17/63/130] |
| Principal Investigators | [name] NIMHANS, Bangalore, India  [name] University of York, UK  [name] University of York, UK |

Contents

[1. Introduction 6](#_Toc66101199)

[2. Study aims 7](#_Toc66101200)

[2.1. Overall aim 7](#_Toc66101201)

[2.2. Objectives 7](#_Toc66101203)

[2.3. Research questions 7](#_Toc66101204)

[3. Overall study design 8](#_Toc66101206)

[4. Intervention Adaptation 8](#_Toc66101208)

[5. Feasibility testing 8](#_Toc66101209)

[5.1. Details of the interventions 9](#_Toc66101210)

[5.2. Study sites and settings 11](#_Toc66101211)

[5.3. Study Population 11](#_Toc66101212)

[5.4. Eligibility 11](#_Toc66101213)

[5.5. Recruitment 12](#_Toc66101214)

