### Details of the interventions

#### Arm 1: Brief advice

Participants randomised to trial arm 1 will receive brief advice (BA) adapted from a community-based trial of tobacco cessation in India.^39^ As part of BA, participants will receive verbal information on the harmful effects of tobacco and will be advised to stop smoking. BA will be delivered by trained psychology graduates in Pakistan and psychology graduates and social workers in India on the same day as enrolment and will last up to five minutes. This will be a one-time interaction: participants in this trial arm will not have any further BA sessions with the psychology graduates and social workers. Participants will be provided with an information leaflet containing the same advice in a written format to take home.

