The behavioural support will include BCTs chosen from a BCT taxonomy from a European context as no similar taxonomy has yet been developed for smoking cessation in LMICs^40^ and will also include BCT previously used for smoking cessation India.^41^ The BCTs will include goal setting, problem solving, social support, information about health consequences and adding objects to the environment. Participants will be encouraged to: (1) reduce smoking to quit, (2) set their own quit dates and (3) make several attempts to quit if their initial attempt fails. The IMPACT 4S intervention has been designed for either face-to-face, remote, or a combination of both face-to-face and remote sessions, to allow adaptation to practical feasibility and participants’ preferences. Remote sessions can be delivered using a number of different options such as telephone or video platforms (e.g. What’s App, messenger, Zoom etc.). The IMPACT 4S Intervention comprises of up to 15 one-to-one counselling sessions, each lasting between 15-40 minutes duration. Each session will be delivered by trained psychology graduates in Pakistan and psychology graduates and social workers in India. Delivery will be facilitated through the use of an intervention manual/guide, a flipbook containing key messages on how to quit smoking, and participants’ resource material. In the case of face-to-face delivery, the manual or flipbook will help intervention delivery staff to deliver messages via photo images on the front of the slides and text on the back of slides and same messages will be reiterated in posters and leaflets. This type of intervention delivery involving face-to-face mode is familiar for health and social workers as well and counsellors in these settings and has been found feasible and acceptable in the TB & Tobacco trial being conducted in Bangladesh and Pakistan.^34^ In order to facilitate the remote delivery of the intervention: 1) an adapted remote intervention manual will be use to deliver the intervention in a way that is consistent with face-to-face sessions; and 2) participants will be supplied with a set of seven-colour coded information sheets in advance that will provide information for each session, including any relevant ‘tasks’ that the participant will be required to complete for each session (e.g. smoking diary, reviewing the checklist for quit day and noting down reasons for stopping.

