### Frequency and duration of follow-up

Following randomisation and baseline data collection, participants in each arm will be followed up at one, three and six months post-randomisation. At each follow-up visit, a trained researcher will administer a structured follow-up data collection form to the trial participant, obtaining information according to the follow-up schedule below (Table 1). The study flow diagram is given in Figure 1 below.

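### Continuous abstinence must fill the whole six-month follow-up, so nearly everyone who quits after the first days counts as a failure, even if they then stay stopped

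*Protocol*

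**What the plan says.** Section 5.14, secondary outcome 1 (repeated in the Summary), is self-reported or carer-reported "continuous smoking abstinence for at least six months (only five instances of smoking allowed during the total six months". It is to be "biochemically verified by CO concentration (CO concentration <7ppm) at six months follow-up". If there is no six-month visit, the latest available visit is used instead.

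Section 5.16 starts the clock at randomisation: "participants in each arm will be followed up at one, three and six months post-randomisation". The Summary gives "Total duration per participant | 6 months", and Table 1 has no later visit.

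Section 5.1 encourages Arm 2 participants to "1) reduce smoking to quit, (2) set their own quit dates and (3) make several attempts to quit if their initial attempt fails". According to the Summary, the sessions are "spread over three/four months". Arm 1 receives its single session "on the same day as enrolment and will last up to five minutes". Section 5.4 admits people who meet "Smoking on >25 days in the past month" and who are willing either to cut down or to quit.

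Secondary outcome 2 is seven-day point abstinence at one, three and six months. Section 5.18 expects 120 measured participants to supply event rates for sizing the definitive trial.

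No section states a grace period, a window counted from the quit date, or the day on which the six months begin.

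**The concern.** The outcome and the intervention run on different clocks. The definition uses up the whole of follow-up, so abstinence has to begin at about randomisation. The Arm 2 programme expects quitting to come later, after a reduction phase, on a date the participant chooses, or at a second or third attempt.

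Other steps also take time. Bupropion follows a referral to a doctor (Section 5.1), and remotely recruited participants may learn their allocation on a later agreed day (Section 5.11).

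The outcome is secondary and will only be described, so no test in this trial is at risk. What is at stake is the rate taken forward. Outcome 1 is the trial's only measure of sustained abstinence. If its rate is used to plan the definitive trial, it leaves out most people who quit during the intervention and stayed stopped.

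**Working it through.** **Inputs from the protocol.** Abstinence of at least 6 months with at most 5 smoking instances (5.14); last visit 6 months after randomisation (5.16, Summary); more than 25 smoking days in the month before entry, so at least 26 (5.4); sessions over three to four months (Summary); 120 measured participants at 30% attrition (5.18).

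**Assumptions not in the protocol.** Six months = 183 days; one month = 30.4 days for conversion; 26 smoking days in 30 at the lightest eligible level; visit on its nominal date; 1 to 10 instances per day. On the lenient reading used here, a slip within the allowance does not restart the window.

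**Step 1. The plan's own figure.** 120 / (1 − 0.30) = 171.4, rounded up to 172. This reproduces the stated enrolment, which the point does not affect.

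**Step 2. Slack in the window.** Follow-up minus required abstinence = 183 − 183 = 0 days.

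**Step 3. Longest abstinence at the six-month visit** = 183 − quit day.

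| Quit day | Days abstinent | Months |
| --- | --- | --- |
| 0 | 183 | 6.0 |
| 7 | 176 | 5.8 |
| 14 | 169 | 5.6 |
| 28 | 155 | 5.1 |
| 91 (3 months) | 92 | 3.0 |
| 122 (4 months) | 61 | 2.0 |

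**Step 4. How far the five-instance allowance helps someone who does not cut down.** Day of the sixth instance = 6 / (instances per day).

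- Lightest eligible level: 6 / (26/30) = 6.9 days
- 5 per day: 6 / 5 = 1.2 days
- 10 per day: 6 / 10 = 0.6 days

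**Step 5. Cutting down first.** Instances used in a straight-line taper over T days = starting rate × T / 2.

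| Taper | Lightest level (26/30 per day) | 10 per day |
| --- | --- | --- |
| 7 days | 3.0 | 35 |
| 14 days | 6.1 | 70 |
| 28 days | 12.1 | 140 |

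The longest taper that stays within five instances is T = 2 × 5 / rate. This is 11.5 days at the lightest level and 1 day at 10 per day.

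**Result.** To qualify, a participant must stop within about the first days, or taper very briefly from a very low level.

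**The case against.** **The source may supply a grace period.** The outcome carries a citation, and Section 5.15 names the Russell Standard. It does so for the CO threshold, however, and the source is not at hand. The intended derivation therefore cannot be known for certain, but the words of Section 5.14 count the total six months and import no grace period.

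**The fallback to the latest available visit gives flexibility.** It covers only participants without a six-month visit. Six months of abstinence cannot be shown at an earlier visit, so the fallback adds ambiguity rather than slack.

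**Arm 2 participants can still qualify.** This stands. A reader might infer that nobody following Arm 2 can meet the outcome. Section 5.1 does not bar an early quit date, and a short lapse followed by a new attempt can stay within five instances. The documents support nearly all who quit later, not everyone in Arm 2.

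**Event rates are available elsewhere.** This also stands. A reader might infer that the pilot cannot supply event rates at all. Point abstinence at six months counts anyone who has stopped by then. Section 5.14 attaches no CO requirement to it, although Section 5.15 verifies self-reported quitters by CO at six months. Section 5.18 refers to event rates of the primary outcome without naming an abstinence measure, while the listed primary outcomes are feasibility measures.

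**The importance is limited.** None of the eight primary outcomes depends on abstinence, and Section 5.18 plans descriptive summaries. That sets the weight of the point but does not remove the conflict.

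**Conclusion.** The conflict is internal to the protocol and the timing arithmetic is firm: a six-month requirement inside a six-month follow-up leaves no slack. A participant who quits at week 4 and never smokes again has about 155 of 183 days and is scored a failure. One who stops at the end of a four-month course has about 61 days. Outcome 1 will therefore understate sustained quitting. This should be corrected, but it does not undermine the feasibility objectives or the enrolment of 172.

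Two further inferences are not supported. A reader might conclude that the definition is biased against Arm 2 by a known amount. Arm 1 receives all its advice on the day of enrolment while Arm 2 is encouraged towards later quitting, so a larger loss in Arm 2 is plausible. Both arms face the same clock, though, and the protocol has no figure for how many in either arm stop at once. A reader might also turn the point into an inflated sample size for the definitive trial. The protocol gives no cessation rates, so such a figure would rest on invented ones.

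The conclusion rests on visits at their nominal dates and on 1 to 10 instances per day. Heavier smoking would only shorten the qualifying period.

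**What to change.** In Section 5.14 and the Summary:

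- State the day on which the abstinence window starts.
- Keep the present strict definition and add beside it a sustained-abstinence outcome with one pre-specified grace period, identical in both arms. For example: no more than five instances between the end of the grace period and the six-month visit, with CO <7ppm at that visit.
- Say how the outcome is classified when there is no six-month visit.

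The length of the grace period is for the trial team to choose. One ending at the three-month follow-up uses an existing visit and needs one added question, on smoking since then. It verifies about 183 − 91 = 92 days, or 3 months. Four weeks would verify about 155 days, or 5 months, but would exclude more of those who quit during the sessions.

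The cost is wording and that question, best settled before follow-up data are collected, because the sustained rate may not be recoverable later. Enrolment is unchanged. The downside is that the verified period falls short of six months and those who quit after the grace period still do not count. With a three-month grace and sessions that may run to month four, some late quitters remain excluded. Participants handled remotely, for whom Section 5.15 says CO cannot be measured, stay unverified under either definition.
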